| Our study design is an open label, outcome assessor blinded randomised controlled trial.  Randomisation: 840 patients will be randomized in a 1:1 ratio using blocks of 6 into the intervention and control groups. Randomisation sequence will be generated by computer software. Allocation concealment is effected via an off-site telephone service maintained by a hospital administrator.  On every working day, the study team members will receive a list of patients who has been readmitted in the past 90 days. The study team members will then screen through the list for eligibility criteria and their LACE scores. For suitable patients, they will be approached and recruited by the research coordinator at the bedside during their hospitalisation. After consent, randomisation will be carried out. Patients allocated to the intervention group are intervened for 90 days and patients allocated to the control group will receive usual care.  Intervention:  The intervention can be divided into 2 parts. Inpatient and outpatient intervention (Appendix 1). The study team is also divided into the 2 teams. Inpatient and outpatient virtual ward (VW) team. The inpatient team is led by an attending family physician, a junior doctor, a nurse case manager, and a part-time (0.1 Full Time Equivalent) pharmacist while the outpatient VW team comprised of an attending family physician and two nurse case managers. A medical social worker who spends 0.5 full time equivalent time in the team supports both the inpatient and outpatient teams.  Inpatient intervention starts when the patient assigned to the intervention is medically stable to be transferred over to the inpatient clinical team. The inpatient team will continue to optimize the patient’s medical conditions and also systematically identify preventable reasons for readmission. Medications will be reconciled with input from the pharmacist and the appropriate community and social services necessary to support the patient’s transition to home will be activated.  Another core component is patient education and coaching. The nurse case managers will use standardized action plans for chronic diseases (examples include congestive cardiac failure, diabetes mellitus, asthma, chronic obstructive pulmonary disease, chronic kidney disease) for patient education. Finally, an individualized care plan complete with written discharge instructions, patients’ appointments, medication changes and the contact information of the outpatient nurse case manager is to be provided to all patients on discharge. The patient’s care is then handed over to the outpatient virtual ward team at the bedside for a seamless information transfer.  At the home setting, the outpatient nurse case manager will follow up with a telephone call within 72 hours of discharge to assess the patient’s condition and ensure adherence to the prescribed care plans and successful activation of community services. This is followed by a home assessment within one week of discharge. During the home assessment, the nurse case manager will assess the patient’s medical condition and health literacy, competency of the care-giver, availability of nursing and home care equipment, adequacy of social support, safety of the home environment and adherence to medication. Each nurse will be in charge of an average of 30 patients at any time during the program.  A multidisciplinary team meeting will be conducted in the morning of every working day. New patients will be discussed and their care plans reviewed. During the meeting, each nurse case manager is to report on the status of patients under her care. Patients who develop urgent deterioration of their chronic conditions and new medical issues will be recalled to the early review clinic to be reviewed by the family physician. Patients who are doing well in the intervention can be reviewed less frequently at the team meetings. Throughout the intervention period, the nurse case managers are contactable during office hours. Scheduled calls to check in on the patients will be made about once a week. Our intervention will last for 90 days after discharge and patients will be discharged at the end of the intervention period to a primary care provider in the community with continuing specialist input as warranted.  Control Group:  Patients in the control group will receive usual medical care provided by the admitting inpatient team of the hospital. On discharge, patients can be referred to primary care provider, specialists in the outpatient clinic and ambulatory community services as considered necessary by the medical team. As part of standard hospital care, patients will receive an abbreviated standardized patient copy of the hospital discharge summary listing their medical diagnoses and medications. For this study, there will be no contact between patients in the control group and the study team throughout the 3-month interval. A scheduled telephone call will be made at the end of the 3-month study period to verify patient outcomes.  Outcomes:  All outcomes are objectively extracted from the hospital electronic health records and the National Electronic Health Records by an assessor blinded to the treatment allocation.  The primary outcome measure is the 30-day unplanned readmission rate.  Other secondary outcomes included:   1. Unplanned readmission rate to any hospital within 90 days, 180 days of discharge, 2. Emergency department (ED) attendance rate within 30 days, 90 days, 180 days of discharge 3. Probability without readmission or death up to 180 days 4. Index admission and post-discharge mortality rate at 90-day 5. Cumulative length of hospital stay at 90 days 6. Number of outpatient specialist clinic visits at 90-day and 180-day |  |

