| **DATA ANALYSIS** |  |
| Data Entry and Storage |  |
| Data entry is made by a trained research co-ordinator into Redcap (Research Electronic Data Capture), a free secure, web-based application designed to support data capture for research studies. Data will be stored in Redcap. Only investigators with access to Redcap can access the data.  **6.2 Data Quality Assurance**  Outcome information will be obtained from the hospital electronic health records and the National Electronic Health Records. Phone follow up will be at 90 days to verify the outcomes information. Information will also be downloaded from routinely used critical care monitors, defibrillators and event records. Public accessible death certificate information will also be reviewed.  Additional steps to ensure data quality includes use of standardized forms, uniform criteria for patient recruitment, internal monitoring of data collection, range checks and verification built into the data entry system and a sequence of logic checking and examination of variables. |  |
| **SAMPLE SIZE AND STATISTICAL METHODS** |  |
| Determination of Sample Size |  |
| We hypothesize that our intervention could reduce readmissions by approximately 25% for patients enrolled in the intervention group. We estimate the baseline readmission rate of eligible patients to be 40% within 30 days of discharge. Based on a power of 80%, level of significance at 5%, and attrition at 10%, a sample size of 420 in each group is required. All statistical analysis will be performed on an intention-to-treat basis. |  |
| **7.2 Statistical and Analytical Plan**  The baseline characteristics will be presented as mean ± SD for continuous variables and frequency counts and percentages for categorical variables. For baseline variables, the 2-sample t-test will be used to compare means and the Pearson chi-square test to compare proportions. A Poisson regression model will be used to obtain relative risks of readmission and ED visits. Kaplan-Meier method will be used to study the survival distribution (based on time to readmission or death) of the intervention and control groups. All tests of significance used 95% level (p<0.05). No subgroup analysis was planned in this study. |  |

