| **DIRECT ACCESS TO SOURCE DATA/DOCUMENTS** The investigator(s)/institution(s) will permit study-related monitoring, audits and/or IRB review and regulatory inspection(s), providing direct access to source data/document.   **ETHICAL CONSIDERATIONS** This study will be conducted in accordance with the ethical principles that have their origin in the Declaration of Helsinki and that are consistent with the Singapore Good Clinical Practice and the applicable regulatory requirements.  This final study protocol, including the final version of the Participant Information and Informed Consent Form, must be approved in writing by the Centralised Institutional Review Board (CIRB), prior to enrolment of any participant into the study.  The principle investigator is responsible for informing the CIRB of any amendments to the protocol or other study-related documents, as per local requirement. |  |
| Informed ConsentConsent will be taken by the research co-ordinators after explaining the study protocol, obtaining voluntary agreement of the participant, explaining the number of visits and alternatives and after the participant is clear of his/her study rights. |  |
|  |  |
| Confidentiality of Data and Participant Records |  |
| Research data and participant database will be stored in Redcap (Research Electronic Data Capture), a free secure, web-based application designed to support data capture for research studies. Data will be stored in Redcap. Only investigators with access to Redcap can access the data.  Once data entry is completed, all identifiers will be subsequently removed from the dataset. No further follow up (more than 90 days) is required. No coded research data will be disseminated to any third parties not involved in the research study. All patient identifiers will be removed from the database to protect patient confidentiality. |  |
| **FUNDING** | |
| This is an investigator-initiated study, and supported by a project grant from the Agency of Integrated Care Singapore (AIC/RPD/RD-OIC/ICCS/010/05-2011). | |

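### The confidentiality section's 90-day end of follow-up contradicts the 180-day time points of secondary outcomes 1, 2, 3 and 6

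*Protocol*

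**What the plan says.** The same six secondary outcomes appear under Hypothesis and Objectives and again under Outcomes in the Study Design section. Four of them reach 180 days:

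- Outcome 1: "Unplanned readmission rate to any hospital within 90 days, 180 days of discharge".
- Outcome 2: "Emergency department (ED) attendance rate within 30 days, 90 days, 180 days of discharge".
- Outcome 3: "Probability without readmission or death up to 180 days".
- Outcome 6: the count of specialist clinic visits, at 90 and at 180 days.

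The other two stop at 90 days: outcome 4 ("Index admission and post-discharge mortality rate at 90-day") and outcome 5 ("Cumulative length of hospital stay at 90 days").

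The section Confidentiality of Data and Participant Records says "Once data entry is completed, all identifiers will be subsequently removed from the dataset" and then, in the next sentence, "No further follow up (more than 90 days) is required".

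Three other statements bear on the point. The Control Group paragraph treats the study period as three months, with a verification call at its end. Section 6.2 says "Phone follow up will be at 90 days to verify the outcomes information". The Outcomes paragraph says that every outcome is taken from hospital and national electronic records by a blinded assessor.

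**The concern.** A 180-day outcome needs information on days 91 to 180, and the confidentiality section says that no follow-up of that length is needed. The parts of the protocol that describe how the study is run point to a 90-day study, while the outcome lists describe a 180-day one. Study staff have to choose which to follow.

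The place of the 90-day sentence makes this more than a slip of wording. It follows the rule on removing identifiers, and finding a patient's later admissions, attendances, clinic visits or death in the records requires an identifier. The protocol gives no date for the end of data entry and does not say that a linkage key is kept. Once the link is gone, the later time points may not be recoverable.

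What is at stake is the question of persistence. The intervention ends 90 days after discharge, so days 91 to 180 are the only period in the plan that could show whether an effect lasts after it stops. Outcome 3 is also the outcome that the Kaplan-Meier analysis in section 7.2 serves. If follow-up ends at day 90, that curve ends there too.

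**Working it through.** **1. Count the time points.** The horizons are those in the two outcome lists, which agree.

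| Secondary outcome | Time points (days) | Number | Beyond day 90 |
|---|---|---|---|
| 1. Unplanned readmission | 90, 180 | 2 | 1 |
| 2. ED attendance | 30, 90, 180 | 3 | 1 |
| 3. Free of readmission or death | 180 | 1 | 1 |
| 4. Mortality | 90 | 1 | 0 |
| 5. Cumulative length of stay | 90 | 1 | 0 |
| 6. Specialist clinic visits | 90, 180 | 2 | 1 |
| **Total** | | **10** | **4** |

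Four of six outcomes are touched, but only 4 of 10 time points (4/10 = 40%). Outcomes 1, 2 and 6 keep 1, 2 and 1 earlier time points. Outcome 3 keeps none.

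**2. Set these against the follow-up statements.** The confidentiality section puts the end of required follow-up at day 90. The three-month study period and the 90-day verification call fit that limit. No section dates an extraction at day 180.

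**3. Work through the unstated date.** Removal of identifiers is tied to completion of data entry, and no day is given. The result therefore depends on an assumption:

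- *Data entry closes at day 90 and identifiers are then removed.* Records cannot be linked for days 91 to 180. All 4 time points are lost, and the readmission-or-death curve stops at day 90. That is 180 − 90 = 90 days, half of the stated 180.
- *Data entry closes only after a day-180 extraction.* All 4 time points can be obtained from the records. The only telephone check is at day 90, so events on days 91 to 180 go without that verification.

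The loss thus ranges from 0 to 4 of the 10 time points. The protocol does not say which case applies.

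**4. Check what is not affected.** The primary outcome is at 30 days, and the sample size rests on it. The inputs in Determination of Sample Size are a control rate of 0.40, a 25% reduction (read as relative, giving 0.40 × 0.75 = 0.30), 80% power, 5% significance (taken as two-sided) and 10% attrition. With the average rate 0.35:

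- Uncorrected: n = [1.96·√(2 × 0.35 × 0.65) + 0.842·√(0.40 × 0.60 + 0.30 × 0.70)]² / 0.10² ≈ 356 per group.
- With continuity correction: n = (356/4)·[1 + √(1 + 4/(356 × 0.10))]² ≈ 376 per group.
- With 10% attrition: 376/0.9 ≈ 418, close to the stated 420.

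No 180-day quantity enters this calculation.

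**The case against.** The strongest reply is that the 90-day sentence concerns patient contact only. All planned contact ends at about that time: the intervention, the control-group call and the verification call. Outcomes come from electronic records, so nothing after day 90 needs the patient. In a trial whose outcome list twice includes 180-day items, data entry would naturally be complete only once those items are entered, so identifiers would still be there when needed.

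Much of this stands, and it rules out several stronger readings that a reader might infer:

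- *That the 180-day outcomes cannot be obtained.* The protocol does not say that identifiers are removed at day 90, and extraction from records remains possible if data entry closes later.
- *That four whole secondary outcomes are lost.* Three of the four keep their time points up to day 90.
- *That a record search to day 180 would go beyond what the ethics board was told.* The 180-day outcomes and their record sources are in the same protocol that the board must approve. At most, the board was given two statements that need reconciling.
- *That the consent wording is out of line.* The consent pages are not available, so this cannot be judged.

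The 90-day call is not a contradiction in itself either. It is a verification step, and record-based outcomes at day 180 can exist alongside it.

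The reply does not remove the conflict. The sentence refers to follow-up, not to contact, and the three-month study period supports the stricter reading. The reading that saves the 180-day time points depends on a closing date that the protocol does not give.

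**Conclusion.** The protocol contradicts itself on the length of follow-up, and the contradiction lies in what it states, not in detail left to an analysis plan. At risk are 4 of 10 secondary outcome-by-time points, including the only one for outcome 3. The loss is total for those four if identifiers are removed before a 180-day extraction. If they are removed afterwards, nothing is lost except telephone verification for days 91 to 180. The first case assumes that data entry closes at day 90, the second that it closes after day 180.

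The 30-day primary outcome, its power and the sample size are untouched. Severity is moderate: no primary conclusion depends on this, but it should be settled before any identifiers are removed, because the loss may not be reversible.

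**What to change.** Replace the 90-day sentence in the confidentiality section with a statement of three things:

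1. Patient contact ends at 90 days.
2. Passive follow-up through hospital, national and death records runs to 180 days after index discharge for all randomised patients.
3. Identifiers are kept until the last patient's 180-day extraction is complete and checked.

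Reconcile the description of a three-month study period with this, and say that the 90-day call verifies events up to day 90 only. Check that the consent wording agrees.

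If longer retention of identifiers is not acceptable, limit outcomes 1, 2, 3 and 6 to 90 days in both outcome lists.

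The cost is a short protocol amendment and longer retention of identifiers. No extra visits or patient contacts are needed.

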Appendix 1: Tasks and Responsibilities of the Inpatient Clinical and Outpatient Virtual Ward Teams

| Functions | Tasks | Responsibility | |
| --- | --- | --- | --- |
|  |  | Inpatient team | Outpatient team |
| 1. Reduce polypharmacy, medication conflicts and error | a. Reconciled medications with pre-admission list | x |  |
|  | b. Identify problem medications (Anticoagulant, anti-platelets, diuretics, insulin & inhalers) | x |  |
|  | c. Review medication use & side effects | x | x |
|  | d. Simplification of medication | x | x |
|  | e. Check on medication adherence within 72 hours after index discharge |  | x |
|  | f. Highlight new/changed/discontinued medication to patient/caregiver & other care providers (Direct communication or discharge summary) | x | x |
| 2. Patient support | a. Initiate ACTION PLANs for high risk diagnosis (Heart failure, Asthma, COPD, renal failure, liver cirrhosis, DM) | x |  |
|  | c. Direct contact information for help given to patient | x |  |
|  | d. Check on ACTION plan adherence within 72 hours after index discharge |  | x |
| 3.Appropriate follow-up | a. Identify primary care provider | x | x |
|  | b. Refer patient to community resources | x | x |
|  | c. Consolidate all patients’ medical appointments | x | x |
|  | d. Arrange review of patients within one week after discharge with memo | x |  |
|  | e. Highlight discharge plan to patient/caregiver & other care providers (Direct communication or discharge summary) | x |  |
|  | f. Home visit within one weeks after discharge |  | x |
|  | g. Monitors patient for deterioration requiring early review |  | x |
| 4. Improve patient & caregiver psycho-social status | a. Screen for depression in patient | x | x |
|  | b. Screen for dementia in patient | x | x |
|  | c. Screen for caregiver stress | x | x |
| 5. Practice of preventive medicine | a. Review reasons for readmission | x |  |
|  | b. Fall risk assessment & prevention | x | x |
|  | d. Recommend appropriate lifestyle modification |  | x |
|  | e. Recommend appropriate vaccination | x | x |
| 6. Palliative care | a. Assess need for advance care planning | x | x |
